### Interventions

#### Group 1: BBL online only (BBL)

Participants in the online only group log on to the trial website weekly to complete an online session lasting approximately 1 h. The 12-week program is detailed in Table 2. The first 7 weeks include the completion of seven educational and individually-tailored behavior-change modules. In the remaining 5 weeks, participants undertake online activities focused on activity and goal monitoring and revision. Tailoring of the five behavior-change modules (weeks 3 to 7) is conducted using an automated algorithm that presents content on the basis of whether or not the particular risk factor the module addresses applies to the participants, as well as on the basis of their responses to several questions measuring psychological determinants of behavior which are presented at the beginning of each of the behavior-change modules. For example, a person who is classified as sedentary on the basis of their responses on the ANU-ADRI, and who does not regard himself/herself as optimistic regarding their prospect of change in the area of physical activity, is presented with information about learned optimism and the relationship between optimism and a range of health outcomes. A physically active person who also regards himself/herself as a role model to others in the area of physical activity will not be presented with information focusing on becoming a role model to others.

**Table 2 T2:** Description of the 12-week online program delivered through the Body Brain Life (BBL) trial website

**Week**	**Activity**	**Description**
1	Module 1: Dementia literacy	The first module focuses on providing participants with general information about dementia including types, onset, symptoms, diagnosis, progression, burden and risk factors (modifiable and non-modifiable). This module serves as an introduction to the subsequent modules.
2	Module 2: Dementia risk factors	This module is aimed at building awareness and knowledge of the various health conditions associated with an increased risk of Alzheimer’s dementia (AD). Specifically, this module provides details regarding the association between AD and several medical conditions (abnormal weight, high cholesterol, diabetes, hypertension, and depression), as well as lifestyle factors (physical activity, nutrition, social and cognitive engagement).

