The program is built in such a way that participants are only able to access the relevant component of the intervention at a given time. The modules become active, one per week, on the same day for the first 7 weeks. Participants are unable to access a newly activated module before completing the previously scheduled module. Each week, participants receive a notification email on the same day alerting them when a new module has become active. The automatic notification system on the trial website is able to detect whether a given participant has not commenced, commenced but not completed, or completed a particular module, and the weekly messages are modified accordingly. Participants receive up to two automatic reminders to complete a module, and this is then followed by a text message, before phone contact is initiated by the study team. As per participation consent agreements, participants who fail to complete a module after these attempts are excluded from the study.

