#### Group 3: Active control (ACON)

The active control group does not access the trial website. Instead, participants in this group receive weekly emails containing links to health-related websites, videos, news items, and so on. The weekly emails contain several links, and participants are encouraged to spend an hour each week browsing through the material. The material is generally organized around the same themes as the ones included in the online BBL program. An effort has been made to include links to informational and educational material but that otherwise does not include the use of identifiable behavior-change techniques which are the ‘active ingredient’ of the BBL program (for example, vicarious reinforcement, anticipated regret, and so on). In addition, other than providing participants with the weekly emails, no further contact is made with the participants in this group, such as reminders and prompts that are delivered to participants in the two experimental groups.

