### Randomization

A permuted block randomization sequence comprising block sizes of 30 stratified by gender is used. The allocation sequence is generated by an independent researcher following the baseline assessments and is not known to the study team at the time of enrollment and baseline assessment.

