### Statistical analyses

Statistical analyses will be based on an intention-to-treat approach. Recent commentary on the best practice for dealing with missing data in RCTs suggests that multiple imputation and Mixed Models are effective approaches and superior to the commonly used techniques like ‘last observation carried forward’ for missing data [25,26]. We plan to use Mixed Models. We hypothesize that BBL + FF > BBL > ACON. The hypothesis that BB + FF > BBL is based on research [27] showing that social milieu and personal contact with researchers are associated with better outcomes in online interventions. There is no empirical evidence on which to base the hypothesis that BBL + FF > BBL in relation to dementia risk reduction per se, due to lack of published data. Results will be exploratory because there are no previous findings in the literature to confirm. There is random allocation to groups so we do not plan to adjust for baseline variables in the primary analysis. In sub analyses we will adjust for baseline measures such as compliance in completing the online modules (in the BBL and BBL + FF groups) by including the number of online modules completed as a fixed effect.

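### A sub-analysis adjusts for the number of modules completed as a baseline measure, although it arises after randomisation and exists only in the two website arms

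*Protocol article*

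**What the plan says.** All references are to the Protocol article.

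- **Statistical analyses.** The general principle is that "Statistical analyses will be based on an intention-to-treat approach", using mixed models. Because allocation is random, "we do not plan to adjust for baseline variables in the primary analysis". In sub-analyses, however, "we will adjust for baseline measures such as compliance in completing the online modules". A parenthesis ties this to the BBL and BBL + FF groups, and the adjustment is made "by including the number of online modules completed as a fixed effect".
- **Randomization.** "The allocation sequence is generated by an independent researcher following the baseline assessments".
- **Group 1: BBL online only (BBL).** "The first 7 weeks include the completion of seven educational and individually-tailored behavior-change modules". A module opens only once the one before it is finished. After reminders, a text message and a phone contact, "participants who fail to complete a module after these attempts are excluded from the study".
- **Group 2: BBL online + face-to-face (BBL + FF).** This arm has the same online program, plus five facilitated group sessions and extra reminder emails for them.
- **Group 3: Active control (ACON).** "The active control group does not access the trial website".

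**The concern.** A baseline covariate is fixed before allocation, so randomisation balances it and adjusting for it leaves the arm comparison valid. Module count has neither property. It is produced during the intervention, it may respond to the arm, and it reflects how motivated the participant is. Calling it a baseline measure puts it in a class of variables for which adjustment is harmless, and so hides the need to say what the adjusted coefficient means.

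Three things are at stake, all within the sub-analysis. A module coefficient could be read as a dose-response effect when it partly measures motivation. A BBL + FF versus BBL contrast could be shifted by conditioning on something the face-to-face sessions may themselves change. The model could also turn out not to be estimable, depending on how the exclusion rule is applied. The article describes the project as a pilot whose data will support a larger trial, so a misread compliance result could carry into that design.

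**Working it through.** **1. Timing and availability.** Baseline assessment comes first, then the allocation sequence, then modules in weeks 1 to 7. The count therefore runs from 0 to 7 and is post-randomisation for everyone who has one. ACON participants have none, because they do not use the website.

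**2. The plan's own figures.** A medium effect is 0.5 SD = 4.25 points, so SD = 4.25 / 0.5 = 8.5. The total of 159 reproduces as a one-way three-group F-test with f = 0.25 and alpha 0.05: power is 0.805 at 159 and 0.797 at 156. The point does not depend on the 159; only the 8.5 and 4.25 are used below.

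**3. Model on the natural reading (BBL and BBL + FF only).** Outcome = b0 + b1 × (BBL + FF) + b2 × (modules completed) + error.

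**4. Excluded participants leave the analysis.** Everyone retained has 7 modules, so the module column is 7 times the intercept column. The design matrix has rank 2 with 3 columns, and b2 cannot be estimated. The arm contrast b1 can still be fitted, but only among completers.

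**5. Non-completers are followed up and kept.** The count varies and the model can be fitted. Least squares gives exactly

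b1 = (difference in mean outcome) − b2 × (difference in mean modules).

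With no true effect, the first term is zero in expectation and the bias is −b2 × (difference in mean modules). It vanishes if completion is equal in the two arms or if b2 is zero.

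To size this, inputs that the article does not give were assumed:
- a standard normal motivation variable U;
- modules ~ Binomial(7, p), with logit p = 1 + U + shift × (BBL + FF);
- outcome = 8.5 × (r × U + √(1 − r²) × noise) at one time point;
- no effect of arm or of modules on outcome.

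A negative r means that more motivated people score lower (less risk). Results for b1, BBL + FF minus BBL, in ANU-ADRI points:

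| r | Equal completion (about 4.9 in both arms) | 4.9 v 5.45 modules | 4.9 v 5.9 modules |
|---|---|---|---|
| 0 | 0.00 | −0.02 | −0.02 |
| −0.2 | −0.02 | 0.43 | 0.78 |
| −0.3 | 0.01 | 0.65 | 1.21 |
| −0.5 | 0.00 | 1.05 | 2.06 |

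Against the target effect, 0.43 / 4.25 = 10% and 2.06 / 4.25 = 48%. Positive values make BBL + FF look worse than BBL, the opposite of the stated hypothesis.

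A repeat run with 1,000,000 participants gave arm contrasts within 0.05 point of these. It also gave b2 with equal completion: −0.73, −1.10 and −1.83 points per module for r = −0.2, −0.3 and −0.5, although modules do nothing in this set-up. Check by the formula for r = −0.2 and shift 0.5, where b2 = −0.76: 0.76 × (5.45 − 4.88) = 0.43.

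**6. If modules do work.** The count then lies on the path from arm to outcome. Adjusting for it also removes whatever part of the face-to-face benefit comes through better completion.

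**The case against.** The best defence has four parts.

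- **The authors know that control has no modules.** The parenthesis limits the count to the two website arms. This stands. A reader might infer a three-arm model with ACON coded 0, where the same simulation gives spurious differences from control of about 3.5 to 11.6 points. The article does not state that coding, so those figures are no evidence against the plan. What remains is that the two-arm model cannot supply a compliance-adjusted comparison with ACON.
- **On the two-arm reading the harm is conditional.** This stands for the arm contrast: it needs both a difference in completion and a link to prognosis, and the article gives figures for neither. A difference is plausible, since BBL + FF has sessions built on the module themes and the article expects personal contact to improve outcomes. The module coefficient needs only the link with motivation.
- **Under intention-to-treat the count varies, so inestimability is not established.** This stands as a limit. If excluded participants contribute baseline data only, the term can be fitted, but the variation in count then sits in baseline scores, which modules cannot have affected. At follow-up everyone still has 7.
- **This is an exploratory sub-analysis.** Correct. A reader might infer that the trial's main message could be inflated or reversed. The article does not support that: the primary analysis is unadjusted, results are called exploratory, and nothing says the adjusted result will be presented as causal.

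**Conclusion.** The point holds for the sub-analysis only. That the label is wrong, and that the covariate is post-randomisation and absent in ACON, follows directly from the text. Bias and inestimability are alternatives, and the article does not settle which applies:

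- If excluded participants leave the analysis, the module term cannot be estimated.
- If they are followed up and kept, the module coefficient is confounded by motivation. The BBL + FF versus BBL contrast is biased to the extent that completion differs between arms and is related to prognosis.

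The illustrative 0.4 to 2.1 points rests on assumed correlations of −0.2 to −0.5 and on a difference in completion of about 0.6 to 1.0 modules. With no correlation, or with equal completion, the arm contrast is unbiased in this set-up. The primary unadjusted comparison is not affected.

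**What to change.** 1. Take module completion out of the baseline covariates, describe it as post-randomisation, and do not adjust the arm effect for it.
2. Report outcome by modules completed within BBL and within BBL + FF as a descriptive, non-causal association.
3. Reconcile the exclusion rule in the Group 1 section with the intention-to-treat statement, so that it is clear whether participants who miss a module still contribute outcomes and to which analyses.
4. If a compliance effect is wanted, pre-specify a complier-average analysis with randomisation as the instrument, for BBL versus ACON only, keeping all randomised participants of those two arms. ACON cannot reach the modules, so non-compliance is one-sided. The analysis still assumes that allocation to BBL acts only through the modules; reminders and contacts are a mild threat to this and should be acknowledged. BBL + FF versus ACON is unsuitable, because the five group sessions offer a route to the outcome that bypasses module count.

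The cost is a change of wording and a small amount of extra analysis. The complier-average estimate will have wider intervals than the covariate adjustment, and it is informative only if non-completers' outcomes are collected. Whether to adjust the primary model for true baseline variables is a separate question.

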### Ethics

The Human Research Ethics Committee at the Australian National University has approved the study protocols and procedures.

### Adverse events

This study evaluates a lifestyle intervention program to reduce risk factors for AD. The target population is adults in mid life who have some of the known risk factors for dementia, but are at the time of the intervention healthy and free of any dementia-related symptoms. We do not anticipate that participants will be placed at a greater risk than that associated with self-driven educational activities over the Internet. Results of screening blood tests are sent to participants’ primary health care providers regardless of their group designation. Furthermore, if any abnormality is detected, a letter is sent to participants to inform them of the presence of the abnormal result and encouraging them to contact their general practitioner for medical advice. To address issues of potential fatigue, the baseline assessment has been kept to a minimum length. In addition, all online and face-to-face sessions were designed in an interactive way and are limited to 1-h sessions (90 minutes for the face-to-face groups). As mentioned above, all online modules are delivered in an individually-tailored fashion to maximize relevance for each individual.

## Discussion

The BBL project is currently under way as an evaluation of the efficacy of a novel intervention in a randomized control trial design. The design of the BBL program aimed to overcome some of the central limitations of similar intervention efforts to date by primarily using a validated AD risk assessment tool, by targeting individuals at late mid life, by developing the intervention content against sound theoretical background, and by choosing an individually-tailored, online delivery format.

The trial, advertised through local radio and newspapers, community clubs, health centers, and noticeboards, generates considerable interest, and to date, approximately one-third of the total target sample has been assessed and randomized into the intervention groups. We anticipate that recruitment will continue until March 2013, and it is estimated that all data collection will be complete by September 2013. The trial has been designed against the Consolidated Standards of Reporting Trials (CONSORT) reporting guidelines [28], and the results of the study are likely to form an evidence base for the feasibility of dementia-prevention campaigns to lead to lifestyle changes and the reduction of dementia risk factors at the population level.

The positive response to the study from individuals who traditionally do not see themselves as the target population for dementia-related studies, most of whom are still in the workforce, reflects community concern regarding dementia risk, and an interest in emerging prevention efforts. Therefore, successful outcomes of the current trial may be associated with actual public health impact upon making the intervention available at the population level. Although additional funds are likely to be required to update and improve aspects of the online intervention program, a particularly strong appeal of this intervention is the fully automated yet individually-tailored online delivery, with negligible maintenance costs.

The study has some limitations. The relatively small sample size limits the possibility of designing more than one control condition, and reduces the feasibility of meaningful long-term follow-up. The study will be underpowered to evaluate the effect (if any) of group within the BBL + FF condition, and this potentially limits the non-independence of the participants. Exploratory analyses of this effect will still be conducted. The project is, however, a pilot project, and the outcome data will form the basis for an application for funding for a larger scale trial. Finally, as is the case for other intervention trials recruiting healthy volunteers, the sample may not adequately represent the general population of those at risk of AD. However the inclusion criteria requiring three or more risk factors mitigates this to some extent. Ongoing efforts are being made to recruit individuals from diverse backgrounds.

## Conclusions

Interventions to prevent or delay the onset of clinical AD and other dementia are urgently needed, and global efforts are beginning to shift in this direction. The BBL trial provides a novel approach to addressing this pressing public health burden.

## Trial status

The trial is ongoing.

## Abbreviations

AD: Alzheimer’s disease; BBL: Body Brain Life; RCT: Randomized controlled trial.
